# Early detection of anaemia in primary care with haemoglobinometry: ANHEMOG clinical trial protocol

**DOI:** 10.1186/s12875-021-01548-z

**Published:** 2021-10-08

**Keywords:** Anaemia, Red blood cell transfusion, Advanced practice nursing, Nurse case manager, Haemoglobinometry, Non-invasive haemoglobin measurement, Primary health care

## Abstract

**Abstract:**

**Background:**

Detecting, treating and monitoring anaemia has a functional, social and economic impact on patients’ quality of life and the health system, since inadequate monitoring can lead to more accident & emergency visits and hospitalizations. The aim of this study is to evaluate the impact in the patient clinical outcomes of using haemoglobinometry to early detect anaemia in patients with chronic anaemia in primary care.

**Methods:**

Randomized controlled trial Capillary haemoglobin will be measured using a haemoglobinometer on a monthly basis in the intervention group. In the control group, the protocol currently in force at the primary care centre will be followed and venous haemoglobin will be measured. Any cases of anaemia detected in either group will be referred to the transfusion circuit of the reference hospital.

**Discusion:**

The results will shed light on the impact of the intervention on the volume of hospitalizations and accident & emergency (A&E) visits due to anaemia, as well as patients’ quality of life. Chronic and repeated bouts of anaemia are detected late, thus leading to decompensation in chronic diseases and, in turn, more A&E visits and hospitalizations. The intervention should improve these outcomes since treatment could be performed without delay. Improving response times would decrease decompensation in chronic diseases, as well as A&E visits and hospitalizations, and improve quality of life. The primary care nurse case manager will perform the intervention, which should improve existing fragmentation between different care levels.

**Trial registration:**

NCT04757909. Registered 17 February 2021. Retrospectively registered.

## Background

The World Health Organization defines anaemia as a condition in which haemoglobin (Hb) concentration is lower than 13 g/dl in men and 12 g/dl in women [1, 2]. The global prevalence of anaemia is 5–10% in patients aged 65 to 70 [3] and 15–25% in patients over 80. Moreover, prevalence ranges from 48 to 60% in patients presenting frailty criteria, according to data from the National Geriatrics Research Consortium and the Beverly Healthcare Data Warehouse [4].

Currently, many patients with chronic anaemia require periodic transfusions. While blood transfusions are safe, they are not exempt from producing adverse effects, so patients must be monitored during the procedure by trained providers who know how to detect and respond to any reactions that may arise and prevent negative clinical outcomes [5] [6]. Several studies recommend making personalized indications for blood transfusions based on the patient’s clinical context, pathologies and preferences rather than exclusively on Hb and haematocrit levels in order to reduce the risks inherent to transfusions. In asymptomatic patients without cardiovascular risks, transfusion is rarely needed until Hb drops below 7–8 g/dl or haematocrit falls between 21 and 24%, although there are some clinical circumstances in which is not recommended to let Hb drop that low for an extended period, or the optimal transfusion strategy is unclear. For example, in patients with coronary artery disease, it has been found that a restrictive transfusion strategy (in most cases, with the limit at 9 mg/dl) is linked to a higher risk of experiencing another cardiac ischemic event, while a personalized, liberal transfusion strategy lowers that same risk [7–11], however, the observed results of a recent clinical trial suggests that there may be merit to a restrictive strategy [7].

Chronic anaemia can lead to multiple decompensations, not just as a result of the disease itself, but also due to its contribution to the adverse development of other chronic pathologies. The prevalence of anaemia in patients with heart failure (HF) is approximately 37% [8], although it can range from 9 to 69.6% depending on the patient’s characteristics. Patients with HF and anaemia present greater cardiovascular risk and higher mortality [2, 3, 8]. Iron deficiency in patients with low ejection fraction is associated with decreased long-term survival and lower quality of life [9].

As for patients with chronic obstructive pulmonary disease (COPD), the incidence of anaemia is estimated to be about 12%, although studies vary, reporting from 7.5–33% depending on patient selection criteria. Moreover, in this group of patients, there is also an association between low haematocrit levels and increased mortality, more hospitalizations and longer average duration of hospital stays [1] . Low Hb in patients with emphysema is also directly linked to mortality. Several studies on the intensive care received by patients with severe COPD and anaemia observed a statistically significant reduction in minute ventilation and the work of breathing, with discharge of respiratory muscles and higher mortality [1, 10]. A study by Sarkar et al. (2015) on COPD patients admitted to intensive care units found that extubation in patients with Hb levels above 12 g/dl was more suitable than in patients with Hb levels below 12 g/dl. In addition to the direct impact anaemia has on the evolution of respiratory diseases and mortality, it also affects quality of life due to the way it limits exercise capacity [1].

Other diseases, such as upper and lower gastrointestinal bleeding, can also lead to chronic anaemia and require transfusions. For those without curative care, therapy most often consists of transfusions to reduce mortality and rebleeding, although they must be based on clinical judgement [11, 12].

Detecting, treating and monitoring anaemia has a functional, social and economic impact on patients’ quality of life and the health system [4], since inadequate monitoring can lead to more A&E visits and hospitalizations [13]. In general, haematocrit and Hb levels are measured in at least 8 ml of venous blood extracted through venipuncture. The blood is transported to a lab where it is measured using automated equipment. There are also portable systems available known as haemoglobinmeters that provide haemogram results in five seconds using just a drop of capillary blood. Clinically speaking, these devices have proven to be accurate and precise in post-anaesthesia care units, intensive care units, hospital A&E and anaemia screening before blood donation [14–16].

Anaemia is a complex clinical issue that often requires coordination between different levels of care. A Nurse Case Manager, is a nurse with a training similar to an Advanced Practice Nurse, and play a crucial role in the communication between primary health care and the hospital level, to ensure the continuity of care and avoiding the defragmentation of the health system [17–19]. The use of haemoglobinmeters by nurse case managers in primary care, on patients with chronic diseases that require regular transfusions would facilitate early detection of low Hb levels and swift inclusion in the adequate hospital circuit for dispensing treatment. This, in turn, would decrease decompensations in chronic diseases requiring extended hospitalization and improve the volume of A&E visits due to this cause [17–19].

The purpose of the present paper is to describe a study protocol for a randomized controlled trial of an intervention directed to early detect anaemia in patients with chronic anaemia through the use of haemoglobinometry in primary care, and thus reduce the number of hospital admissions compared with the standard surveillance of anaemia.

## Methods/design

### Research question

Monthly capillary Hb measurement with a hemoglobinometer improves patient outcomes compared to standard venipuncture monitoring in chronically anemic patients?

### Main objective

Compare the number of hospitalizations due to anaemia of patients receiving monthly capillary Hb measurements and those receiving standard venipuncture monitoring.

### Secondary objectives

Compare the number of hospital A&E visits due to anaemia of patients receiving monthly capillary Hb measurements and those receiving standard monitoring.

Compare changes in quality of life of patients receiving monthly capillary Hb measurements and those receiving standard monitoring.

Assess satisfaction with monthly haemoglobinometer measurements.

### Hypothesis

The research hypothesis is that periodic measurements taken by the nurse in primary care using the haemoglobinometer will decrease the number of A&E visits and hospitalizations and improve quality of life as compared to standard venous Hb measurements.

### Design

Randomized controlled trial number NCT04757909.

### Sample

#### Setting

Catalan Health Institute primary care centres in Santa Coloma de Gramenet, Badalona and Mataró (Barcelona, Spain).

Inclusion criteriaPatients over 40 who had two or more transfusions of packed red blood cells due to chronic anaemia in a year.Patients’ whose primary care health provider is the Catalan Institute of Health.

Exclusion criteriaPatients with kidney failure receiving haemodialysis treatment.Patients receiving palliative care.Patients presenting moderate to severe cognitive impairment, with a score of 5 or higher on the Pfeiffer questionnaire and who do not have a caretaker capable of detecting signs of decompensation in the patient.

The study procedure is explained in the Consolidated Standards of Reporting Clinical Trial (CONSORT) flow chart (Fig. 1) [20].

**Fig. 1 Fig1:**
[figure not shown]
CONSORT Study Flow Chart

#### Sample size

The sample size was calculated at 138 patients, 69 in both the control and intervention group, thus making it possible to detect a difference in hospitalization of 25% (60% in the control group and 35% in the intervention group, based on the disposable information in the database of the health provider). This sample size also takes into account an alpha risk of 0.05, a beta risk below 20% and a 10% dropout rate, with bilateral comparison. The arcsin approach was used for this calculation.

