### Statistical analysis

Statistical analyses will be conducted on a blinded intention-to-treat basis, with all participants who were initially randomised into the study included where data are available for each measurement time point.

Univariate descriptive statistics:

The main numerical variables will be described by measures of centrality and dispersion or absolute and relative frequencies in the case of categorical variables. Univariate comparisons between the intervention group and control group will be performed using mean comparison tests (T-test or similar) or distribution comparison tests (Chi-squared or similar).

Predictive model:

The result variables will be considered discrete quantitative variables. Multiple linear regression will be used to model the data collected, taking those that present significant differences in the previously calculated univariate models as independent variables, in addition to the demographic and clinical variables considered relevant.

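### The 138 patients are sized on the proportion hospitalised, but the stated main outcome is the number of hospitalisations, so the stated power is not shown to apply to it

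*Protocol article*

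**What the plan says.** The Sample size section of the protocol article sizes the trial to "detect a difference in hospitalization of 25% (60% in the control group and 35% in the intervention group". It allows for "an alpha risk of 0.05, a beta risk below 20% and a 10% dropout rate", is two-sided ("with bilateral comparison"), and names the arcsine approach. The result is 69 per arm, 138 in total. The section speaks of hospitalisation in general. It attaches neither a restriction to anaemia nor a time window to the two percentages.

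Elsewhere the outcome is a count:

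- **Main objective:** "Compare the number of hospitalizations due to anaemia of patients receiving monthly capillary Hb measurements", set against standard venipuncture monitoring.
- **Intervention:** in the control group, record review and two-monthly telephone calls establish how often each patient was admitted during the study.
- **Expected results:** the first main result variable is again the number of anaemia admissions.
- **Statistical analysis:** "The result variables will be considered discrete quantitative variables", to be modelled by multiple linear regression. Univariate group comparisons are described generically, as tests of means (t-test or similar) or of distributions (chi-squared or similar).

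No section defines having at least one hospitalisation as an outcome. None gives a mean, standard deviation or rate of admissions per patient.

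**The concern.** The arcsine method compares two proportions, so the calculation treats each patient as either hospitalised or not. A comparison of counts is a different test. Its power depends on the mean and the spread of admissions per patient in each arm, and two percentages do not determine these. The only power statement in the document thus belongs to a comparison that the document does not name as its main one.

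Two things are at stake. If the count is analysed and no difference is found, the result could be read as an adequately powered negative when nobody has established that it was. A reader also cannot tell whether success means fewer patients admitted or fewer admissions, so the choice could be made after the data are seen.

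**Working it through.** **Inputs from the Sample size section:** 0.60 and 0.35, two-sided alpha 0.05 (z = 1.960), power 80% (z = 0.842), dropout 10%.

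**1. The plan's own figure.**

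- h = 2·asin(√0.60) − 2·asin(√0.35) = 0.506
- n per arm = 2(1.960 + 0.842)² / h² = 61.3, rounded up to 62
- With dropout: 62 / 0.9 = 68.9, rounded up to 69 per arm, 138 in total
- Power at 62 per arm: Φ(0.506·√(62/2) − 1.960) = 80.4%

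The 138 is correct for a comparison of proportions.

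**2. Power for a comparison of mean counts, 62 evaluable per arm.** With arm means m₀ and m₁, variances v₀ and v₁, and d = m₀ − m₁:

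power = Φ( d / √((v₀ + v₁)/62) − 1.96 )

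The documents supply none of the means or variances. The distributions below are therefore assumptions, each chosen so that 60% and 35% of patients have at least one admission.

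*Same admissions per admitted patient in both arms* (mean μ, SD s). For a proportion p admitted, the arm mean is pμ and the arm variance is p(s² + μ²) − (pμ)².

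| μ, s | m₀, m₁ | v₀ + v₁ | Power |
|---|---|---|---|
| 1, 0 (exactly one each) | 0.60, 0.35 | 0.4675 | 82% |
| 1.5, 1.0 | 0.90, 0.525 | 2.002 | 55% |
| 2, 1.5 | 1.20, 0.70 | 4.008 | 50% |

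For example, in the second row: 0.375 / √(2.002/62) = 2.087, and Φ(2.087 − 1.96) = 0.55.

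*Poisson or negative binomial with the same dispersion k in both arms.* The mean is −ln(1 − p) for Poisson and ((1 − p)^(−k) − 1)/k otherwise. The variance is m + k·m².

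| k | m₀, m₁ | Rate ratio | Power |
|---|---|---|---|
| 0 (Poisson) | 0.916, 0.431 | 0.47 | 91% |
| 1 | 1.50, 0.538 | 0.36 | 94% |
| 2 | 2.625, 0.683 | 0.26 | 95% |

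Simulated t-tests (20,000 runs each) for these three cases gave 91%, 97% and 99%. The approximation does not overstate power here. The high power goes with a large assumed effect on the mean.

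**3. Reading the results together.** The same 60% and 35% fit count power well below, close to or well above 80%. The stated power carries over, roughly, in the special case of one admission per admitted patient.

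**The case against.** **The chi-squared wording leaves room for a binary test.** The Statistical analysis section allows frequencies for categorical variables and a chi-squared or similar test, and a test of hospitalised yes/no would fit. It does leave that room. But the wording is generic and never dichotomises hospitalisation, and the same section then classes the result variables as discrete quantitative and fits a linear model. It does not fix a binary main analysis.

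**This is a condensed article, and the SAP is not shown.** Mapping endpoints to tests is often left to such documents, and a SAP may choose between the two readings. The sizing basis, objective, outcome and scale of analysis are nevertheless all stated here, and they do not agree.

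**The trial need not be underpowered.** This objection stands. A reader might infer that repeat admissions must pull power below 80%, but the documents do not support that. Standard rate models give more than 80%, and one admission per admitted patient gives 82%. Eligibility requires two or more transfusions in a year, not two or more admissions, and no section reports admissions per patient. The low figures also depend on the assumed spread: zero-truncated Poisson counts with means 1.5 and 2 (SD 0.75 and 1.09) give 65% and 62% instead of 55% and 50%. They further assume that the intervention leaves admissions per admitted patient unchanged, whereas the article expects fewer decompensations generally.

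**Conclusion.** The mismatch is real. The arithmetic behind 138 is right for the proportion hospitalised, but the stated main outcome is a count, and the beta risk below 20% is not shown to apply to it. To say that the stated power definitely fails for the count would go too far, since it nearly carries over in one special case.

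On the assumptions shown, power for the count with 62 per arm is about 50-55% if admitted patients average 1.5 to 2 admissions in both arms, 82% if each has exactly one, and 91-95% under Poisson or negative binomial rates matching 60% and 35%. These are illustrations, not bounds. A mean of 2.5 with variance 6 among admitted patients, for instance, gives 39%. The direction is undetermined, because the document gives no mean or variance of admissions. The power statement needs correcting because it is the only one the trial has for its main objective.

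**What to change.** Name one primary analysis before the data are analysed, and make the Main objective, Sample size, Statistical analysis and Expected results sections agree with it.

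- **Option (a): proportion primary.** Define the primary endpoint as the proportion of patients with at least one anaemia hospitalisation over a stated follow-up period, reported as a risk difference with 95% CI. First confirm that the 60% and 35% refer to anaemia admissions over that period, since the Sample size section says neither. Keep 138 and make the count secondary.
- **Option (b): count primary.** State in the Sample size section that the 80% power applies only to the proportion hospitalised. Restate power for the count from the mean and variance of admissions per patient. Take these from the provider database behind the 60% if it holds them; otherwise show power over a range of plausible values.

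Adding a binary analysis beside the count without ranking them would leave two competing main tests.

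The cost is a database query, where the data exist, and some rewritten text. Neither option needs extra patients. The price of (b) is that the restated power may be less favourable than 80%, and the trial would then accept that shortfall openly. For scale, 80% power in the 55% and 50% scenarios would take about 125 and 140 per arm after dropout: 2.002 × 7.849 / 0.375² = 111.7, so 112, and 112/0.9 gives 125; 4.008 × 7.849 / 0.50² = 125.8, so 126, and 126/0.9 = 140.

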#### Assigning patients to interventions

Patients will be randomly assigned to the control or intervention group using a list of numbers with a random computer-generated allocation to control or intervention in an adjacent column.

#### Data collection, management and analysis

Data will be collected at the monthly visits of participants in the intervention group and the bimonthly visits of participants in the control group.

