### Intervention

The Hb levels of participants in the intervention group will be taken once a month with a Veri Q® haemoglobinometer, that showed good performance data, in accuracy test compared with the reference value from Nihon Kohden MEK-6420 (R2 = 0.9881) and with the Sysmax reference value (R2 = 0.9968) [21]. If a patient’s haemoglobin level falls below their reference value, the nurse case manager will activate the transfusion circuit by scheduling an urgent referral to the day hospital, an outpatient service where short-term treatment and diagnostic tests are performed. The interdisciplinary team at this unit will prescribe and administer the transfusion and handle the hospital discharge, in a specific circuit between health levels created to this intervention.

The WHOQOL-BREF questionnaire on quality of life will be administered at the first visit and six and 12 months.

To know the satisfaction with the intervention, a single item survey will be administered upon inclusion in the study and six and 12 months. The question is “to what extent are you satisfied with your anemia control”, and the possible answers are not satisfied, satisfied and very satisfied.

An ad hoc satisfaction survey on the intervention will be administered upon inclusion in the study and six and 12 months.

Participants in the control group received standard monitoring, the frequency of which is variable, since it is determined by clinical criteria. The data will be collected by reviewing patients’ computerized clinical records and a bimonthly phone call to determine how many times they have been hospitalized and visited the A&E during the study period. The WHOQOL-BREF questionnaire on quality of life will be administered at the first visit and six and 12 months of inclusion in the study. Data will also be collected for the control group.

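### As written, hospitalizations and A&E visits are collected by different modes and at different intervals in the two arms, which can bias the primary comparison in either direction

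*Protocol article*

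**What the plan says.** The main objective is a between-arm comparison of a count: "Compare the number of hospitalizations due to anaemia of patients receiving monthly capillary Hb measurements and those receiving standard venipuncture monitoring". A&E visits due to anaemia are the first secondary objective, and both counts head the list of main result variables under Expected results.

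Two sections of the protocol article describe how the data are obtained:

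- In the section Data collection, management and analysis, the article states: "Data will be collected at the monthly visits of participants in the intervention group and the bimonthly visits of participants in the control group".
- In the control-group paragraph of the Intervention section, the data come from a review of "computerized clinical records and a bimonthly phone call to determine how many times they have been hospitalized and visited the A&E during the study period".

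For the intervention arm, the Intervention section describes the monthly contact ("The Hb levels of participants in the intervention group will be taken once a month with a Veri Q® haemoglobinometer") and the questionnaires. It names no record review or phone call specifically for that arm.

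On blinding, the Statistical analysis section states: "Statistical analyses will be conducted on a blinded intention-to-treat basis". The article does not describe who decides, or with what knowledge of the arm, whether an admission was due to anaemia.

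**The concern.** When two arms are compared on a count of events, the events must be looked for in the same way in both. Here the text sets a different contact interval for each arm. Under the Intervention section it also sets a different mode: face-to-face contact in one arm, records and a telephone call in the other. An admission found in one arm might go unrecorded in the other, so the counts could differ without any effect of the intervention.

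Two features add to this. Patients and nurses know the allocation, because monthly finger-prick testing is visibly different from usual monitoring. The endpoint also counts only admissions attributed to anaemia, and that attribution involves judgement in patients with other chronic disease. Both the primary outcome and the first secondary outcome are exposed.

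The two sections also contradict each other: the control contact is a visit in one and a phone call in the other.

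**Working it through.** **1. The two descriptions side by side**

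| | Intervention arm | Control arm |
|---|---|---|
| Data collection section | monthly visits | bimonthly visits |
| Intervention section | monthly contact; record review not clearly stated | record review plus bimonthly phone call |

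Bimonthly most likely means every two months. If it meant twice a month, the interval would still differ from monthly. So the frequency differs under either reading, and the mode differs under the Intervention section.

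**2. Reproducing the plan's own figure**

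Inputs, all from Sample size: "60% in the control group and 35% in the intervention group", two-sided alpha 0.05, power 80%, 10% dropout, arcsine method.

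- h = 2·asin(√0.60) − 2·asin(√0.35) = 1.7722 − 1.2661 = 0.5061
- n per arm = 2·((1.960 + 0.842)/0.5061)² = 61.3, rounded up to 62
- With dropout: 62/0.90 = 68.9, rounded up to 69 per arm, 138 in total

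This matches the stated 138. Power at 62 evaluable per arm is Φ(h·√(62/2) − 1.960) = Φ(2.818 − 1.960) = 80.4%.

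**3. What unequal capture would do**

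The documents give no detection rates, so the shares missed below are assumptions. Observed proportion = true proportion × (1 − share of hospitalized patients missed in that arm). Power and rejection rates use the same arcsine formula with 62 per arm, both tails.

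*No true effect, 60% in both arms, one arm misses some and the other none.* Worked case at 10%:

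- 0.60 × 0.90 = 0.54, so the spurious difference is 6 points
- h = 1.7722 − 1.6509 = 0.1213, and h·√31 = 0.675
- Rejection rate = Φ(0.675 − 1.960) + Φ(−0.675 − 1.960) = 10.4%

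| Share missed in one arm | Spurious difference | Rejection rate (nominal 5%) |
|---|---|---|
| 5% | 3 points | 6.3% |
| 10% | 6 points | 10.4% |
| 20% | 12 points | 26.9% |

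If the common rate is 35% instead, the rejection rates are 5.5%, 7.0% and 13.4%. The sign of the spurious difference depends on which arm misses events.

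*True rates 60% and 35%.* Worked case with controls missing 10%: 0.54 − 0.35 = 0.19; h = 1.6509 − 1.2661 = 0.3848; Φ(0.3848·√31 − 1.960) = Φ(0.182) = 57.2%.

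| Share missed | If controls miss: difference, power | If intervention arm misses: difference, apparent power |
|---|---|---|
| 5% | 22 points, 69.8% | 26.8 points, 85.6% |
| 10% | 19 points, 57.2% | 28.5 points, 89.8% |
| 20% | 13 points, 31.4% | 32 points, 95.5% |

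These figures treat the outcome as hospitalized yes or no, as the sample size calculation does. The stated outcome is a number of admissions. A patient with several admissions drops out of the proportion only if all of them are missed, so missing 10% of patients is not the same as missing 10% of admissions.

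**The case against.** The strongest reply is that the record-review sentence may cover both arms. It refers to patients in general, and the paragraph ends by adding that data will also be collected for the control group, which reads oddly if everything before it concerned controls only. If the same records are searched for everyone, capture of admissions could be nearly complete and the bias small. This is a fair reading. However, the sentence sits in the control-group paragraph and is joined to a phone call described only there, so the text does not settle the matter. Attribution to anaemia would still be open to knowledge of the arm.

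A second reply is that a journal article condenses the full protocol, so code lists and adjudication rules may sit elsewhere. That stands: their absence is not the finding. The finding rests on the arm-specific collection that the article does state, and on its two conflicting descriptions. The stated blinding of the analysis does not establish that outcomes are classified blind.

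A reader might also infer more than the documents support:

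- *That control admissions are lost through phone recall.* Controls have record review as well as the call, so an admission is lost only if both miss it.
- *That the assessor or the recall period differs by arm.* The article does not say who collects outcomes in either arm. It puts the nurse case manager in charge of the intervention process, not of outcome recording. The call is said to ask about events over the study period.
- *That no later analysis could correct the bias.* A common record extract for both arms would largely cure the capture problem.
- *That the bias favours the intervention.* More frequent contact could find more events in the intervention arm; record review named only for controls could find more there.

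**Conclusion.** The point holds as a possible bias of undetermined direction and unknown size. As written, the primary outcome and the A&E outcome are ascertained by different modes and at different intervals in the two arms, in a trial without blinded treatment and with an endpoint that needs a judgement of cause. The two sections also cannot both be followed for controls.

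The 6-point spurious difference, the rejection rate of about 10%, and the fall in power from 80% to 57% all rest on an assumed 10% of hospitalized patients missed in one arm. They show how sensitive a trial of this size would be and do not estimate what will happen. The sample size of 138 is not in error and stands if ascertainment is the same in both arms.

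This is more than missing detail. It concerns the primary outcome, and the remedy uses a source on which the protocol already relies.

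**What to change.** - Take hospitalizations and A&E visits in both arms from the same computerized clinical records, over the same window from randomisation to 12 months. The 12 months is inferred from the questionnaire schedule and should be stated.
- Apply one written rule for attribution to anaemia to the pseudonymized extract, with the arm label removed.
- Use visit or phone reports only as prompts to check the records, asked at the same interval in both arms.
- Reconcile the Data collection section (visits) with the Intervention section (phone call), and state whether record review covers both arms.

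An analysis of all-cause admissions from the same extract is optional.

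The cost is wording in the protocol and analysis plan, and one record extract for the intervention arm. No extra patients or study visits are needed; a prompt at a common interval could be a phone call. The downside is that admissions outside the provider's records would be caught only through the prompts.
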